## Materials and methods

### Participants

#### Study setting

Participants will be identified and enrolled in the general population of the Tuscany region, in Italy. The frontline and non-frontline healthcare professional groups will be identified by health workers belonging to any health professional category working in Covid-19 units and in other units in Tuscany (i.e., any other type of healthcare setting, working with any type of patients and any type of pathological condition). The university students will be identified and recruited among the undergraduate populations of the Tuscany Universities of Siena, Florence, and Pisa. Older people (aged ≥65 years old) will be identified and recruited in different contexts in Tuscany including associations for leisure activities of senior citizens, community services and volunteer associations for older people in Tuscany. Older people will be considered eligible if they are not hospitalized in any healthcare facility or a nursing home. The entrepreneurs/dealers will be identified and recruited among those who operate in Tuscany in the economic sectors most affected by the pandemic such as the tourism and hospitality sectors (i.e., hotels) and commercial establishments including fitness industries (e.g., gyms, beauty centers) which were forced to close during some of the phases of the pandemic and still are affected by the extremely slow recovery of the economy.

#### Eligibility criteria

Individuals will be included in the study if: (a) they are adults residing in Tuscany (aged ≥18 year old), (b) they belong to one of the risk above mentioned groups of the general population (i.e., healthcare professionals working in Covid-19 units or other units, university students, older people, entrepreneurs/dealers), (c) they have a smartphone with an Internet connection and are able to use it and/or have experience in the use of smartphone applications, (d) they can read written texts in Italian language, I they do not have any self-reported medical or neuropsychiatric conditions which can interfere with the use of a smartphone app or can make it difficult to understand the materials contained in the app (e.g., intellectual disabilities, sensory deficits, neurological pathologies, severe psychiatric conditions in the acute phase such as an ongoing acute depressive, bipolar or psychotic episode).

### Intervention

#### Intervention description

Participants will be allowed to use the contents of the app daily for a total period of four months from the baseline assessment, according to a frequency and duration at their discretion within this period. The app will contain written and audio-visual materials inspired by evidence-based psychoeducation and cognitive behavioral exercises and techniques, which have already been demonstrated to be effective in promoting well-being and preventing stress by randomized controlled trials and meta-analyses (Spek et al., 2007; Carlbring et al., 2011; Simon et al., 2019; Kladnitski et al., 2020).

App material will consist of (1) psychoeducation readings and audio-visual materials about emotions and the so-called cognitive distortions (i.e., mental traps that act as factors of vulnerability and maintenance of psychological stress), (2) (ABC, “*Activating Event – Beliefs – Consequences*”) diaries of recording of automatic thoughts, emotions and behavior’s (an example of an ABC diary completed by a fictional healthcare worker is presented in Table 1), (3) cognitive restructuring cards for the identification of cognitive distortions and modification of negative automatic thoughts, (4) problem-solving cards applied to daily critical situations, (5) audio exercises for meditation and distancing from automatic thoughts for the management of negative emotions, (6) factsheets on the construction of personal values. The examples of the diary and problem-solving cards applied to daily critical situations will be different for each target group and tailored to their needs and daily experiences. These materials, indeed, will be adapted to the stress-related aspects of the pandemic (e.g., perception of vulnerability, benefits and costs of preventive actions, negative consequences of social distancing in daily life, measures to deal with the pandemic on a daily basis, economic gain) emerged through focus groups conducted online with representatives of the included populations.

**Table 1 tab1:** Example of an ABC daily diary completed by a fictional healthcare worker (Mario).

**ACTIVATING EVENT** *Where? When? What?*	**MY AUTOMATIC THOUGHTS** *What was going through my mind?*	**MY FEELINGS** *How did I feel?*	**MY PHYSICAL SENSATIONS** *Where I was feeling those sensations in my body*	**MY BEHAVIOURS** *What I did in response to thoughts, feelings and physical sensations*
** *MARIO* **	*Too many visits today*	*Anger*	*Fatigue*	*Try to answer patients’ questions, meet their requests as much as possible and be concentrated over job tasks*
** *(50 years old, family physician)* **	*I am not prepared to cope with this stressful situation… alone on the frontline*	*Helplessness*	*Headache*	*Complain about colleagues*
*During the last months since the pandemic beginning, there has been an increased number of visits, patients seeking help, phone calls at office*	*Even tonight, when I get home, I could infect my family members*	*Anxiety*	*Muscle tension*	*Extend the work shifts*
		*Sense of guilt*	*Shortness of breath*	*Avoid rest, family life and leisure time*
				*Worry every night*

#### Strategies to improve adherence to interventions

One of the main issues regarding self-management interventions delivered by mobile apps is the risk of sub-optimal adherence, i.e., a minimal or less frequent use of the app. Such utilization of the application could limit the effectiveness of the intervention. To enhance participation and a regular use of our app, users will be guided in the compilation of the diary by an easy-to-follow step-by-step process and a reminder will be sent to them through mobile notification and email. Moreover, during the phase of data analysis, sub-optimal adherence will be controlled by including the frequency of use of the app (measured with the number of weekly accesses and mean duration of accesses) as a covariate in the ANCOVA model.

Another issue that mobile apps must face concerns the risk of relatively high drop-out rates. In a recent meta-analysis of randomized controlled trials conducted in adult samples, Linardon and Fuller-Tyszkiewicz (2020) found a drop-out rate of 24.1% at short-term follow up and 35.5% at longer-term follow up for mobile applications with rates varying according to target mental health conditions. In another meta-analysis (Torous et al., 2020), drop-out rates could reach 48%, when accounting for publication bias, in apps targeting participants with depressive symptoms. Basing on this evidence, we expect a similar range of dropout rates for our sample.

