#### Statistical methods for primary and secondary outcomes

Normality of the variables will be detected by Kolmogorov–Smirnov test. A series of repeated measures ANCOVAs will be performed to assess the effectiveness of the smartphone app on the outcomes. The baseline scores on the scales will be entered in the statistical model as covariates, the type of target group as a factor and the scores for each timepoint as dependent variables, respectively. Effect sizes will be calculated as Squared Eta indices (η^2^) according to the formula provided by Olejnik and Algina (2003). Following Cohen et al. (1998), effect sizes of 0.01, 0.06, and 0.14 will be interpreted as small, medium, and large, respectively. The statistical significance will be set at *p* < 0.05.

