#### Methods in analysis to handle protocol non-adherence and any statistical methods to handle missing data

Missing baseline data will be treated by multiple imputation (Sinharay et al., 2001). Missing longitudinal data will be managed through an intention-to-treat analysis with the last observation carried forward technique (Newell, 1992). The statistical analyses will be carried out by the software SPSS version 25.00.

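### App use is chosen by participants after baseline, so entering it as an ANCOVA covariate does not control adherence: it changes what is estimated and can remove group differences that run through use

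*Protocol article*

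**What the plan says.** All places are in the Protocol article.

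- **Strategies to improve adherence to interventions.** During data analysis, "sub-optimal adherence will be controlled by including the frequency of use of the app" as a covariate in the ANCOVA model, use being "measured with the number of weekly accesses and mean duration of accesses". The same section warns that low use could limit how well the intervention works.
- **Intervention description.** Participants may use the app for four months after baseline, "according to a frequency and duration at their discretion within this period".
- **Statistical methods for primary and secondary outcomes.** Effectiveness is assessed by repeated measures ANCOVAs: "The baseline scores on the scales will be entered in the statistical model as covariates, the type of target group as a factor". App use is not mentioned.
- **The section on non-adherence and missing data.** Its heading reads "Methods in analysis to handle protocol non-adherence and any statistical methods to handle missing data". The text gives this rule: "Missing longitudinal data will be managed through an intention-to-treat analysis with the last observation carried forward technique".
- **Objectives.** Differences between the target populations in app usage and in effectiveness will be explored.
- **Plans for assessment and collection of outcomes.** All data come in through the app.

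Nowhere is the use-adjusted model called exploratory or secondary.

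**The concern.** A baseline covariate can sharpen an estimate without changing its meaning. App use is a different kind of variable. It arises after baseline, the participant decides it, any benefit of the app has to pass through it, and distress or its relief may alter it. A model that holds use fixed no longer asks how much scores changed, or how groups differed, among those enrolled. It asks what remains between people who happened to use the app equally.

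At stake is chiefly the comparison of target groups. If one group benefits more because it uses the app more, that is a real difference in effectiveness, and adjustment would hide it. The time effect can also change meaning, depending on how the covariate is coded. The coefficient of use can pick up an artefact from the missing-data rule. Finally, a reader cannot tell which of two models gives the effectiveness result.

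**Working it through.** **Inputs from the article.** N = 1,800; visits at baseline and at 2, 4 and 6 months; dropout of 24.1%, 35.5% and up to 48%; LOCF; outcomes collected in the app. The article gives no figure for the effect of adjusting for use, so there is none to reproduce.

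**Assumed inputs (not in the article).** Baseline-to-outcome correlation 0.5; the use-outcome slopes and group difference in use stated below; a common drift over six months of 0 to -0.5 SD; random dropout with equal hazard per visit; recorded use that stops at dropout.

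**Step 1: which model applies.** The adherence section puts use into the ANCOVA. The statistical methods section lists baseline scores and target group only. It does not say that the list is complete, so the two can be read cumulatively, but neither refers to the other.

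**Step 2: group contrast.** Total contrast = direct part + (slope per SD of use) × (group difference in use). With no direct part:

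- unadjusted: -0.3 × 0.5 = -0.15 SD
- adjusted for use: 0.00

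Precision with 900 per group: the residual variance given baseline is (1 - 0.5²) + 0.3² = 0.75 + 0.09 = 0.84. SE = 2 × √0.84 / √1,800 = 2 × 0.917 / 42.43 = 0.0432. Then z = 0.15 / 0.0432 = 3.47, and power = Φ(3.47 - 1.96) = Φ(1.51) ≈ 93%. Simulation gives 93% unadjusted and 7% adjusted, close to the nominal 5%. Centring use does not help here.

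**Step 3: reverse direction.** If the app does nothing but change in the outcome drives use (assumed link 0.3), the use slope is about 0.21 SD in absolute size and significant in 100% of simulated trials.

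**Step 4: time effect.** Suppose change = -0.1 SD per weekly access, with mean use of 3.

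- at mean use: -0.1 × 3 = -0.30 SD
- at zero use: -0.1 × 0 = 0.00

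Entered uncentred, use makes the time test refer to the second line (4% to 5% of trials significant). Mean-centred, the test refers to the first (100%, as without adjustment).

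**Step 5: use together with LOCF, no effect of use.** Let d be dropout by month 6, s = (1 - d)^(1/3) the retention per visit, and let a drift of -0.3 SD accrue in three equal steps. The mean LOCF change is then -0.1 × (s + s² + s³). The last two columns are simulated (month-6 score on baseline and use, 400 replicates).

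| Dropout | s | Mean LOCF change (true -0.30) | Use coefficient per SD | p < 0.05 |
|---|---|---|---|---|
| 24.1% | 0.912 | -0.1 × (0.912 + 0.832 + 0.759) = -0.250 | -0.036 | 46% |
| 35.5% | 0.864 | -0.1 × (0.864 + 0.747 + 0.645) = -0.226 | -0.051 | 75% |
| 48% | 0.804 | -0.1 × (0.804 + 0.647 + 0.520) = -0.197 | -0.064 | 89% |

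The rate depends mainly on the assumed drift. Over 24.1% to 48% dropout:

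| Common drift | False significance of use |
|---|---|
| 0 | about 5% |
| -0.1 SD | 10% to 18% |
| -0.2 SD | 21% to 60% |
| -0.3 SD | 49% to 90% |
| -0.5 SD | 90% to 100% |

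Repeat simulations gave 7% to 22% for the -0.1 row and 46% to 92% for the -0.3 row. On observed month-6 scores at -0.3 SD the rate is 5% to 7%. With use unrelated to dropout, LOCF leaves it at about 6%. If scores worsen on average, the sign reverses and more use looks harmful.

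**The case against.** Several stronger readings are tempting, and the article does not support them.

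- **That adjustment removes the effect of the app.** There is no control arm, so no between-arm effect can be adjusted away; the endpoint is change over time. The loss in Step 4 comes from coding and vanishes with mean-centring, which the article neither specifies nor excludes. It also depends on model details left open. With four visits and the baseline score also entered uncentred (baseline mean assumed 2 SD), the time test is significant in 100% of trials. This objection stands for the time effect. It does not touch Step 2.
- **That the covariate breaches intention-to-treat.** That phrase is attached to missing longitudinal data, and a covariate excludes nobody. The analysis set is unchanged; what changes is the quantity estimated.
- **That LOCF plus use must produce a dose-response.** It can. It needs a non-zero average change and recorded use that falls with dropout. The second is likely, because outcomes are collected in the app, although researchers may contact non-responders. The first is unknown.
- **That the use coefficient will be read as benefit.** The article speaks only of controlling for use and never says that the coefficient will be tested or interpreted.
- **That the sections flatly contradict each other.** They can be read as adding up. That is loose cross-referencing, but it still leaves the effectiveness model undefined on this point.

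**Conclusion.** The concern holds in a limited form. Use is post-baseline, self-selected and on the path from app to outcome, so adjusting for it does not do what the article says it will. This follows from the text and needs no simulation. The firmest consequence concerns the comparison of target groups: under the assumed inputs a true contrast of -0.15 SD is reported as 0.00, and its chance of detection falls from 93% to about the nominal level. The result scales with the group difference in use and with the slope. If groups use the app equally, adjustment removes nothing from the contrast.

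The shift of the time test to zero use is conditional on uncentred coding. The false use coefficient is conditional on LOCF, on use falling with dropout and on a drift that the article does not give. It would be wrong to infer that the planned analysis must miss an effect or must create a dose-response. The simulations in Step 5 cover the month-6 visit, not the full repeated measures model.

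**What to change.** 1. Delete the sentence that adds app use to the ANCOVA. State one effectiveness model for all enrolled: baseline score as covariate, target group, visit, and group by visit. This reconciles the adherence section with the statistical methods section.
2. Report app use (weekly accesses and mean duration) descriptively by target group. That serves the usage part of the objective directly.
3. If a relation between use and outcome is wanted, place it in a separate exploratory analysis, labelled associational, on observed rather than LOCF scores. The 5% to 7% error rate found for observed scores assumes random dropout, so the label matters there too.

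The cost is a change of wording and one extra exploratory analysis, with no new data. The fix does not make the result causal: with a single group and no control, change over time still cannot be attributed to the app.

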### Outcomes

The effectiveness of the mobile app will be evaluated on the following outcomes: (i) perceived susceptibility and severity of the pandemic situation, perceived benefits, and costs of preventive health behavior’s (such as using a mask), (ii) knowledge about Covid-19 preventive behavior’s and negative consequences of social distancing, (iii) stress and psychopathological symptoms (i.e., anxiety, depression, and post-traumatic stress symptoms) and cognitive distortions.

These variables will be measured at a baseline assessment (i.e., each participant will complete the questionnaires within 2 weeks before using the app), at an intermediate evaluation (i.e., 2 months after the baseline evaluation), at a post-test evaluation (i.e., 4 months after the baseline evaluation), and at a follow-up evaluation conducted 6 months after the baseline assessment. The endpoint consists of the variation in depressive, anxious and stress states, cognitive distortions, and coping strategies, from the baseline to the intermediate, post-test and follow-up evaluations. The scores in all questionnaires that measure the endpoints will be aggregated in the form of mean scores with relative standard deviations at every evaluation. No harm derived by the use of the self-help application is expected.

#### Participant timeline

Table 2 shows the participant timeline.

**Table 2 tab2:** Participant timeline.

[figure not shown]

#### Sample size

According to an *a-priori* power analysis, at least 1,800 participants are required to conduct a repeated measures ANCOVA with between-within factors and interactions to estimate a medium effect size on each one of the outcomes with 95% power and a significance level set at 0.05.

#### Recruitment

Participants’ enrolment will last for 2 months. During participants’ recruitment, a series of meetings will be organized, respectively in the healthcare services, universities, tourism and fitness industry associations, older people’s associations, to disseminate the study’s aims, and encourage participation. A website will be created to disseminate the study’s aims and online brochures about the study will be sent to the email addresses of Department directors of healthcare services, representatives of university students, representatives of industry associations and representatives of elderly associations, respectively. Eligible participants will be emailed the link through which they can download the smartphone application.

### Data collection, management, and analysis

#### Plans for assessment and collection of outcomes

All the data will be collected through the mobile application: each participant will be invited to compile the questionnaire at the above mentioned timepoints. Outcomes will be measured by the scores on the following psychometric scales: Depression Anxiety Stress Scale-21 (DASS-21; Lovibond and Lovibond, 1996), Cognitive Distortions Scale (CDS; Covin et al., 2011) and Coping Orientations to Problems Experiences -New Italian Version (COPE-NVI-25; Foà et al., 2015). An overview of the study tools is presented in Table 3.

**Table 3 tab3:** Study tools.

**Measure**	**Construct and item**	**Psychometric proprieties**
Depression anxiety stress scale-21 (DASS-21; Lovibond and Lovibond, 1996)	It measures stress, anxiety and depression symptoms. 21 items.	Good convergent and discriminant validity and high internal consistency in English (Daza et al., 2002; Norton, 2007) and Italian (Bottesi et al., 2015) samples.
Cognitive distortions scale (CDS; Covin et al., 2011)	It measures the frequency of cognitive distortions in two domains: interpersonal and personal achievement. 20 items.	Excellent overall reliability in English (Covin et al., 2011) and Italian (Aldi et al., 2020) samples.
Coping orientation to problems experiences – New Italian version (COPE-NVI-25; Foà et al., 2015)	It assesses the coping styles in difficult or stressful situations. 25 items.	Good to excellent reliability across the scales in the Italian sample Foà et al. (2015).
Self-report questionnaire related to the health belief model	The perception of vulnerability/severity with respect to the Covid-19. The perception of the benefits/disadvantages of health/preventive behaviors with respect to the	

The DASS-21 is a 21-item questionnaire that measures one-week state negative affect, developed with the specific aim of achieving maximal differentiation between the affective symptoms of depression, anxiety, and tension/stress. Respondents indicate the extent to which they experienced each of the symptoms depicted in the items during the previous week on a 4-point Likert-type scale between 0 (*Did not apply to me at all*) and 3 (*Applied to me very much, or most of the time*). The factor structure of the DASS-21 is stable, and its scales showed good convergent and discriminant validity and high internal consistency in clinical and in non-clinical samples and in different ethnic groups in adults (Daza et al., 2002; Norton, 2007). The Italian version (Bottesi et al., 2015) demonstrated good internal consistency.

The CDS (Covin et al., 2011) is a measure that individually assesses the frequency with which respondents experience 10 cognitive errors in interpersonal and achievement domains. Covin et al. (2011) examined the validity and reliability of the scale in a non-clinical sample and found an excellent overall reliability (*α* = 0.85), acceptable reliability coefficients for the two subscales (Interpersonal subscale, *α* = 0.75; Achievement subscale, *α* = 0.79). The Italian version (Aldi et al., 2020) showed a single factor with excellent reliability (*α* = 0.96).

The COPE-NVI-25 was developed by Foà et al. (2015) with the aim to assess the coping styles adopted by subjects in difficult or stressful situations. This is a short version of the COPE (Carver et al., 1989). The COPE-NVI-25 showed as good psychometric skills as those shown by the original version. It is capable to evaluate coping strategies in a hospital context, where a simple and fast assessment is often required; it is proved to be an instrument as valid as the original COPE, but easier to administer. The COPE-NVI-25 is a multi-dimensional inventory that assesses individual differences in coping styles. It is comprised of 25 items, which are rated on a 4-point scale ranging from 1 (I usually do not do this at all) to 4 (I usually do this a lot). The instrument includes five subscales corresponding to five different coping styles: Social Support (example item: “*I seek moral support from friends and relatives*”), Avoidance Strategies (example item: “*I admit to myself that I cannot deal with it, and quit trying*”), Positive Attitude (example item: “*I try to learn something good from experience*”), Problem Solving (example item: “*I focus on dealing with this problem and, if necessary, I put from other things aside*”), and Turning to Religion (example item: “*I try to find comfort in my religion*”). A higher score on a particular subscale indicates a greater use of that specific coping strategy. In the present study, the scores for each one of the COPE-NVI-25 scales were calculated by summing the scores obtained by the participants on the items that were related to the target scale in the validation study. The reliability indices were good to excellent across all the COPE-NVI-25 scales (Social Support scale: Cronbach’s alpha = 0.80; Avoidance Strategies scale: Cronbach’s alpha = 0.72; Positive Attitude scale: Cronbach’s alpha = 0.90; Problem Solving scale: Cronbach’s alpha = 0.86; Turning to Religion scale: Cronbach’s alpha = 0.96).

Additional endpoints include the scores on a self-report questionnaire that will address the following areas: the perception of vulnerability/severity with respect to the Covid-19 infection (example item: “*How much risk do you feel about getting Covid-19 infection?*), the perception of the benefits/disadvantages of health/preventive behavior’s with respect to the Covid-19 infection (example items: *“How beneficial were health/preventive behaviours?”; “How disadvantageous?”*).

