#### Plans to promote participant retention and complete follow-up

The patients will receive extensive information about the study set-up and requirements during the recruitment. The importance of completion of the follow-up will be stressed. Patients are allowed to stop at any time during the study and are not obliged to give a reason to discontinue. If possible, the patient will be asked to complete the survey at 2, 4 and 6 months after inclusion. Questionnaires are completed using the mobile app, and therefore participants can do this at any convenient moment. All patients are reminded throughout mobile app notifications to fill out the questionnaires. Throughout the follow-up period, the researchers will check responses and if necessary, contact participants for completion of their follow-up.

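### The app under test is the only stated route for outcome questionnaires, so participants who remove it risk having no later outcomes

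*Protocol article*

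**What the plan says.** **Collection route.** Under Plans for assessment and collection of outcomes, the protocol article states: "All the data will be collected through the mobile application". Plans to promote participant retention and complete follow-up repeats this: "Questionnaires are completed using the mobile app, and therefore participants can do this at any convenient moment". No other route is named.

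**Reminders and contact.** The retention section says: "All patients are reminded throughout mobile app notifications to fill out the questionnaires". Just after noting that participants may stop at any time, it adds: "If possible, the patient will be asked to complete the survey at 2, 4 and 6 months after inclusion". It also provides that "the researchers will check responses and if necessary, contact participants for completion of their follow-up". The adherence section (Strategies to improve adherence to interventions) mentions reminders by notification and email, but in connection with the diary and regular use of the app.

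**Timing.** Intervention description: "Participants will be allowed to use the contents of the app daily for a total period of four months from the baseline assessment", with frequency and duration left to the participant. The Outcomes section places the last assessment later: "at a follow-up evaluation conducted 6 months after the baseline assessment".

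**Email.** Recruitment: "Eligible participants will be emailed the link through which they can download the smartphone application". The trial therefore holds email addresses.

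**Design, dropout and missing data.** Trial design gives a single group without control. The adherence section cites dropout of 24.1% (short term), 35.5% (longer term) and up to 48%, and expects a similar range here. The section on missing data fills missing longitudinal values by last observation carried forward (LOCF) under an intention-to-treat label.

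**The concern.** The intervention and the measuring instrument are the same piece of software. A participant who deletes the app stops being exposed and, on the route described, also stops being measurable. Notifications no longer arrive, and someone reached by a researcher would still have to reinstall the app to answer. The exposed window includes the two months between the end of the use period and the 6-month assessment.

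In a single-group before-after design the result is a within-person change, so it depends directly on who supplies later data. There is no control arm in which similar losses might partly cancel. If keeping the app is related to how a participant fares, outcomes will be missing for reasons connected with the outcome. LOCF then replaces those outcomes with an assumption that nobody can check, because the people who left the app were never measured.

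**Working it through.** **1. Is there a second route?** The two sections on data collection agree that questionnaires are completed in the app. The reminders specified for questionnaires are app notifications. The email reminders in the adherence section concern app use. Researcher contact is a prompt to complete follow-up, and no form outside the app is attached to it. So no second route is stated.

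**2. Who is exposed?**
- Stops using the contents but keeps the app: still receives notifications and can still answer.
- Removes the app: receives no notifications, may be contacted, and must reinstall to answer.

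The risk attaches to removal, not to low use as such.

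**3. How many outcomes could be missing from all causes?** Inputs: 1,800 participants (Sample size) and the three cited dropout rates. Missing = 1,800 × p:
- p = 0.241: 434
- p = 0.355: 639
- p = 0.48: 864

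These are total dropout. The article does not say what share would be due to in-app collection.

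**4. What does the planned LOCF do with them?** Let responders change by D, let a fraction p be missing, and let baseline be the value carried forward. The LOCF mean change is (1 − p)D, that is 0.759D, 0.645D and 0.52D. What non-responders truly do is an assumption in each case below.

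*(a) No change in non-responders.* True mean = (1 − p)D, the same as LOCF. Bias is 0% at every p.

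*(b) Half the responders' benefit.* True mean = (1 − p/2)D. LOCF divided by truth:
- 0.759 / 0.8795 = 0.863, understated by about 14%
- 0.645 / 0.8225 = 0.784, understated by about 22%
- 0.52 / 0.76 = 0.684, understated by about 32%

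*(c) Worsening, for illustration by 0.25D.* True mean = (1 − 1.25p)D. LOCF divided by truth:
- 0.759 / 0.69875 = 1.086, overstated by about 9%
- 0.645 / 0.55625 = 1.160, overstated by about 16%
- 0.52 / 0.40 = 1.30, overstated by 30%

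*(d) Relapse after a gain.* If non-responders had gained g at 2 months, that value is carried forward, and they have truly returned to baseline by 6 months, then LOCF = (1 − p)D + pg against a truth of (1 − p)D. The overstatement is pg / [(1 − p)D], which is positive for any g > 0.

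The sign of the bias therefore depends on the unmeasured course of the people who left. Outcomes collected from them would settle it.

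**The case against.** **Stopping the intervention is not the same as leaving measurement.** This stands. A reader might infer that everyone who stops using the app loses their outcomes. The article does not support that: contents are used at discretion, a lapsed user who keeps the app can still answer, the survey is to be requested at each follow-up if possible, and researchers may contact non-responders. These measures reduce the problem. They do not supply another place to answer.

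**Inflation of the effect is not established.** This also stands. A reader might compute the overstatement as 1/(1 − p) − 1, which gives 32%, 55% and 92%, by assuming no change in non-responders. Those figures describe a mean over responders only, which is not the planned analysis. Under LOCF with baseline carried forward the same assumption gives no bias.

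**The link to benefit is inference.** The article nowhere says that those who keep the app are those who improve. People who feel better may also delete it. The adherence section says only that low use could limit effectiveness.

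**The dropout rates are not caused by the collection route.** They come from meta-analyses of app trials and cover all reasons, and the 48% concerns apps for depressive symptoms. Some people would ignore an emailed link too.

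**The article is condensed.** A full protocol might say how contacted non-responders answer. But this article does more than omit an alternative: it states positively that all data come through the app.

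**Conclusion.** The point holds as a risk built into the data collection plan. As written, outcome capture depends on keeping the app under test, and the stated safeguards only partly offset that. In a single-group trial expecting dropout of about 24.1% to 48%, this can make missingness depend on app use.

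Neither the size nor the direction of any bias can be fixed from the article. With baseline carried forward, LOCF is unbiased if non-responders do not change, understates by about 14%, 22% and 32% if they have half the responders' benefit, and overstates if they worsen or lose a gain that was carried forward. These results rest on the assumed course of non-responders and treat all expected dropout as missing. The share due to the collection route is unknown. The change is still worth making, because it is cheap and replaces part of an uncheckable assumption with observed outcomes.

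**What to change.** Amend Plans for assessment and collection of outcomes and Plans to promote participant retention and complete follow-up as follows:

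- Provide a web version of the same questionnaires.
- Email every enrolled participant a personal link at 2, 4 and 6 months, whether or not the app is still installed or used.
- Keep the in-app version as an alternative.
- Record the mode of completion for each assessment, so that outcomes can be compared by route.
- State that researchers who contact non-responders will offer the web link.

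**Cost.** One web form, automated emails to addresses the trial already uses, and a short protocol amendment notified to the ethics committee. No visits or extra staff are needed. There are two small downsides. The same self-report scales would be completed in two modes. Emailed responses would also have to be linked to study records in a way that fits the anonymity promised under Ethics and dissemination, for example through a coded link. The article's Trial status section places recruitment after this protocol version, so on that schedule the change could be made before enrolment.
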